### Aim and objectives

The primary aim of this study is to evaluate whether total hemoglobin measures using the Masimo SpHb continuous non-invasive monitoring device are accurate as compared to gold standard CBC laboratory tests using peripheral venous blood samples. To achieve this aim, three statistical objectives were identified:

1.To estimate the level of deviation and agreement between SpHb and CBC values longitudinally.2.To calculate the level of agreement between SpHb and CBC values among binary (healthy versus anemic) and ordinal (mild, moderate, severe anemia versus normal) measures longitudinally.3.To describe sociodemographic and clinical factors affecting the difference between SpHb and CBC values.

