### Study sample

**
*Recruitment of participants*
**

A sample of 900 pregnant women from each site will be selected from the PRISMA study primary cohort, for a total of 2700 participants. Participants may be recruited sequentially through household-based or facility-based pregnancy surveillance (e.g., the first 900 women enrolled in PRISMA will also be included in this study from the date of protocol approval per site).

**
*Eligibility criteria*
**

Any participant that is eligible for the PRISMA study is also considered eligible for this study. However, research staff may exclude women from the study, based on the presence of injury, deformity, tattoo, or birthmark that interferes with Masimo sensor placement or performance or a finger size that does not appropriately fit the device. Presence of henna, nail polish or long nails is not an exclusion criterion, but staff will record information about these factors as they might interfere with the Masimo device performance.

**
*Consent*
**

PRISMA MNH uses a multiphase process to recruit women through pregnancy surveillance. Consent or assent will be obtained from pregnant women after a pre-screening process to determine eligibility in the PRISMA MNH study.

**
*Study status*
**

The parent PRISMA MNH study began recruiting and enrolling pregnant women on 22 September 2022 (Pakistan), 23 November 2022 (Kenya), and 15 December 2022 (Zambia). The study is planned to complete enrollment at the end of 2025. 

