### Objective 3: Factors affecting differences between SpHb and CBC

In order to assess factors that might affect the accuracy of SpHb, we will include the following characteristics in linear mixed models in order to assess differences between paired SpHb and CBC measurements. These variables will be collected during the enrollment visit, ANC visit, and or during the postpartum visit.

Maternal age,Anemia severity stratum,Nutritional status (e.g., iron deficiency),HIV status (Zambia and Kenya sites only),Malaria status (Kenya site only),Helminth infection status (Kenya site only),Gestational age at assessment and at first ANC visit,Technician,Time between SpHb collection and CBC collection,Participant’s early pregnancy BMI (measured at first ANC visit),Mid upper arm circumference (MUAC),Study site,Tobacco use,Estimated plasma volume (PV)
^
17
^ where Kaplan-Hakim formula
^
18
^ estimates PV as: 

PV(cPV)=(1−hematocrit)∗[a+(b∗weightinkg)]

Where,
*a = 1,530* in males and
*864* in females, and

*b = 41* in males and
*47.9* in females.

We will assess differences between these subgroups as follows:

*Candidate forms of the differences in hemoglobin levels (outcome):*

Differences (
*Δ* =
*SpHb*–
*CBC*),Absolute differences |
*Δ*|,Log(SpHb) - log(CBC) = log(SpHb/CBC).

*Comparison of the outcomes across different categories:*

Contingency tables will be constructed where the distribution of the outcome (differences) will be compared across different levels of the risk factors. For example, mean/SD/IQR of the outcome will be listed side by side for each site and p-values using mixed models comparing the distributions between different locations will be reported.

*Plot of the outcome versus risk factors:*

Lowess or kernel smoothing curves will be fitted for the relationship between the outcome and continuous risk factors such as true Hb values.

*Univariate analysis of candidate risk factors:*

One linear mixed model will be fitted for each candidate risk factor. Candidate risk factors will be tested one at a time and marginal associations between the size of measurement errors and each risk factor will be reported as change per sample SD or change w.r.t. reference level, 95% confidence interval and p-values. All effect sizes and CI can be reported in a forest plot

*Multivariate analysis of selected candidate risk factors:*

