Elastic net penalized regressions (R package glmnet) with cross validation selected tuning parameters will be employed to select a set of harmonious and prognostic covariates. One multivariate linear mixed model will be fitted with control of the collinearity (VIF <8) and manual tuning using clinical knowledge. The predictive accuracy of the final model will be assessed using R
^2^ and residual plots.

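### Objective 3 measures the predictive accuracy of its final mixed model by R-squared with no held-out women named; this is fit, not prediction, and could look high when no covariate predicts anything (minor)

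*Protocol article*

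**What the plan says.** The multivariate part of *Objective 3: Factors affecting differences between SpHb and CBC* has three steps.

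1. Selection: "Elastic net penalized regressions (R package glmnet) with cross validation selected tuning parameters will be employed to select a set of harmonious and prognostic covariates". Cross-validation is mentioned here only, for choosing the tuning parameters.
2. Refit: "One multivariate linear mixed model will be fitted with control of the collinearity (VIF <8) and manual tuning using clinical knowledge".
3. Assessment: "The predictive accuracy of the final model will be assessed using R" (squared; the superscript follows), together with residual plots.

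No hold-out sample, outer cross-validation loop or optimism correction is named. The article does not say whether R-squared refers to the fixed part or to the full fitted values.

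Two other statements set the limits of the point. Confidence intervals and p-values are promised for the one-factor-at-a-time models, whose effects are "reported as change per sample SD or change w.r.t. reference level, 95% confidence interval and p-values"; none are promised for the multivariable model. The purpose given under *Aim and objectives* is descriptive: "To describe sociodemographic and clinical factors affecting the difference between SpHb and CBC values".

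**The concern.** Predictive accuracy means how well the model forecasts the SpHb error in a woman it has not seen. R-squared on the rows that chose and fitted the model does not measure that, for two reasons.

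- **Random intercept.** Each woman contributes several visits. A mixed model's fitted values normally include her estimated random intercept, which is learned from her own SpHb-minus-CBC differences. For a new woman it is unknown. An R-squared that counts it credits the covariates with variation they do not explain.
- **Selection and tuning.** Covariates chosen because they fit these data, and then adjusted by hand, will fit these data somewhat better than new ones.

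What is at stake is how Objective 3 is read. A sizeable R-squared presented as predictive accuracy would suggest that the listed factors account for much of the device's error when they might account for almost none.

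**Working it through.** **Plan's own figure.** The article gives no R-squared, power or precision for the multivariable model, so there is none to reproduce for this point. Its main sizing figure concerns the mean shift and checks out: 900 pairs at 0.108 SD, one-sample t-test, two-sided 0.05, give power 0.899 against the stated 90%.

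**Inputs from the article.** Five time points (*Study design*); 900 women per site, 2700 in all (*Study sample*); 15 listed candidates, counting the two gestational-age variables separately, and more parameters once technician, site and severity are coded as categories.

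**Assumptions.** A random intercept per woman, and a within-woman correlation ρ of the differences of 0.2, 0.4 or 0.6. The article gives neither.

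**1. R-squared from full fitted values when no covariate has any effect.** Scale the total variance to 1, with m visits.

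- Variance of a woman's mean: V = ρ + (1 − ρ)/m.
- Shrinkage of her estimated intercept: k = ρ/V.
- Residual variance around k × (her mean): 1 − 2kV + k²V.
- Hence R² = kV(2 − k) = ρ(2 − k).

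| ρ | V (m = 5) | k | R² = ρ(2 − k) | R² in new women |
|---|---|---|---|---|
| 0.2 | 0.36 | 0.556 | 0.29 | 0 |
| 0.4 | 0.52 | 0.769 | 0.49 | 0 |
| 0.6 | 0.68 | 0.882 | 0.67 | 0 |

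Simulation of the planned pipeline (2700 women, 5 visits, 20 candidates) gave the same three values, and 0.00 in new women. The result does not depend on having exactly five visits. *Sample size considerations* speaks of three repeated measures; with m = 3, k is 0.429, 0.667 and 0.818, and R² is 0.31, 0.53 and 0.71.

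If the covariates do explain a share F, the same statistic is F + (1 − F) × ρ(2 − k). With F = 0.10 and ρ = 0.4 it is 0.10 + 0.90 × 0.49 = 0.54, so a true 10% would be shown as 54%.

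**2. R-squared from the fixed part only.** Simulated selection and refit, assuming three effects of 0.15 SD, four of 0.04 SD, covariate correlation 0.3, ρ = 0.4, five visits and folds formed on rows:

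| Women | Parameters | Same data | New women | Optimism |
|---|---|---|---|---|
| 900 | 20 | 0.150 | 0.130 | 0.020 |
| 900 | 40 | 0.159 | 0.121 | 0.038 |
| 2700 | 20 | 0.144 | 0.138 | 0.006 |
| 2700 | 40 | 0.145 | 0.133 | 0.012 |

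A separate simulation with 2700 women, 20 candidates and participant-level folds put the optimism at about 0.003. The range is therefore about 0.003 to 0.04. Manual tuning and VIF pruning were not simulated; they could add to it by an unknown amount.

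**3. Intervals after selection, if they are reported.** Coverage of nominal 95% intervals for null covariates that were selected was 56–75% in simulations with no effect or a single effect, and about 88–94% with seven true effects. Truly associated covariates in the seven-effect setting had about 92–98%. A model with no selection covered the nulls at about 95%.

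**The case against.** The strongest reply is that this is loose wording on an exploratory aim. The article does not say that random intercepts will be counted, and the split between fixed-part and full R-squared is ordinary analysis-plan detail that may exist elsewhere. On the fixed-part reading the optimism is trivial at this sample size. That the same data are used throughout is inferred from no other data being named. All of this stands, and it is why the point is minor. It does not remove it, because the article names the measure of predictive accuracy, and on neither reading does that measure assess prediction.

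Three stronger readings are tempting and not supported.

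- **A reader might infer that the final model's confidence intervals are too narrow.** The article promises none for that model; those it promises belong to the univariate models, where nothing is selected. If intervals were reported, under-coverage would fall mainly on falsely selected covariates, with a size that depends heavily on how many factors truly matter. Nor do simulated false-positive counts show harm. At least one null covariate was nominally significant after refit in 42–51% of simulated studies, but an unselected 20-term null model would give about 1 − 0.95²⁰ = 64%.
- **A reader might infer that selection should be dropped for one model with every candidate.** HIV status is listed for Zambia and Kenya only, and malaria and helminth status for Kenya only. A pooled complete-case model with all of them would keep Kenya alone and leave site inestimable. The number of technicians is not stated, and plasma volume is computed from hematocrit and weight, so it overlaps with other candidates. Selection against a full model is a debatable trade-off here.
- **A reader might infer that the model will be used to correct SpHb readings.** The article proposes no such use.

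**Conclusion.** The point holds for the assessment step. R-squared and residual plots, with no held-out women named, measure fit and cannot support a statement about predictive accuracy. The size depends on a choice the article leaves open. With random intercepts in the fitted values, R-squared would be about 0.29 to 0.67 with five visits when no covariate predicts anything; this rests on the assumed correlations of 0.2 to 0.6 and a random-intercept model. With the fixed part only, the overstatement is about 0.003 to 0.04 before any effect of manual tuning. The concern about intervals is conditional on their being reported. Severity is minor: Objective 3 is descriptive, and Objectives 1 and 2 do not use this model.

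**What to change.** Replace the sentence on predictive accuracy with wording such as: *Predictive performance will be reported as R-squared and RMSE of the fixed-effect prediction, obtained by participant-level cross-validation (or a participant bootstrap) in which elastic-net selection and the mixed-model refit are repeated in each fold or resample. The share of variance due to the random intercept will be reported separately.* Keep the residual plots as a check of model assumptions.

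Label the selected model exploratory. If confidence intervals or p-values are given for it, either state that they are not adjusted for selection or bootstrap the whole procedure by participant.

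Manual tuning cannot be fully repeated in each fold. Fix the clinical decisions on which terms to force in or leave out before the data are seen.

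The cost is a short resampling loop, some advance agreement on the clinical choices, and a lower reported R-squared. No data collection or sample size changes.

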### Sample size considerations

**
*Total sample size*
**

The total sample size of 900 per study site will give 90% power for site-specific analyses to detect a systematic shift (defined as mean difference between each pair of SpHb and CBC divided by the standard deviation of all paired differences) of size 0.108 between the mean of SpHb measurements and the mean of CBC measurements. That is, if the SpHb system shifts from the reference CBC measurements by 10.8% of the SD of the mean difference, the probability that we will detect such a systematic shift using one sample t-test with significance level 0.05 is 90%. The total sample size of 900 will also give 80% power to detect a systematic shift of size 0.093*SD between the mean of SpHb measurements and the mean of CBC measurements. The SD can be calculated in the same way as those in the Bland Altman plots. However, 900 is a very conservative estimate of the sample size and would be sufficient to analyze the three sites independently. Based on our pilot data from Kenya and Pakistan, the mean difference between SpHb and CBC is approximately 0.8 times its SD; even a sample size as small as 19 pairs would provide 90% power using one-sample t-test.

In detecting the extreme differences (i.e. large absolute value) between the SpHb and CBC measures on the same sample, the sample size of 900 will give 99.99% probability to detect the top 1% largest values in the distribution of all differences. It will also give 98.90% probability to detect the top 0.5% largest values in the distribution of all differences, and 93.31%, 83.50%, 59.36% probability to detect the top 0.3%, 0.2%, 0.1% largest values in the distribution of all differences, respectively. With three repeated measures from each of the 900 participants, the listed probabilities are conservative estimates of chances in catching extreme values.

**
*Strata sample size*
**

In cases where the distribution of differences between SpHb and CBC measurements differs in specific anemia strata, we speculate power and sample size for each stratum. Assuming the difference in the hemoglobin measurements of matched pairs is normally distributed with standard deviation SD, and the Type I error probability is set at 0.05, the relationship between the required sample size in the stratum and the detectable alternatives in the unit of SD is plotted above. If the true difference in the mean response of matched pairs is 0.8*SD, we will need to study 19 pairs of subjects to be able to reject the null hypothesis that this response difference is zero with probability (power) 0.90. When the mean difference is 0.5*SD, we would require a sample size of 33 pairs in the strata.

**
*Repeated measures*
**

The power of 90% can be achieved with 19 paired SpHb and CBC measurements in a cross-sectional study. We plan to collect repeated measurements from 19 participants at different time points. The longitudinal design will provide a power greater than 90%. Furthermore, longitudinal data also provide us opportunities to study the discrepancy or degree of agreement between SpHb and CBC at specific gestational age, given there are 19 matched pairs of data at any given time.

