**Methods and analysis:**

The proposed prospective cohort will be nested within the ongoing Pregnancy Risk and Infant Surveillance and Measurement Alliance (PRISMA) Maternal and Newborn Health (MNH) study. Three study sites (located in Zambia, Kenya, and Pakistan) will participate and collect hemoglobin data at five time points (<20 weeks, 20 weeks, 28 weeks, 36 weeks’ gestation, and six weeks postpartum). We will measure hemoglobin using a venous blood sample via hematology auto-analyzer complete blood count (gold standard) and the non-invasive device. The primary objective is to assess agreement between Masimo total hemoglobin and complete blood count and on a continuous scale using Intraclass Correlation Coefficient and Bland-Altman Analysis. The second objective is to assess agreement between the two measures on a binary scale using Positive Percentage Agreement and Negative Percentage Agreement, Cohen’s Kappa, and McNemar Test. On an ordinal scale, agreement will be measured using Weighted Cohen’s Kappa and Harrel’s Concordance Index. Lastly, we will assess factors that might affect the accuracy of Masimo total hemoglobin using linear mixed models.

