### Data quality control

**
*Equipment standardization and calibration*
**

All laboratory measurements will be conducted according to standardized operating procedures (SOPs) internally developed for the parent study. Specifically, research staff and laboratory technicians will follow exactly the Laboratory SOP, Maternal Clinical SOP, Infant Clinical SOP, and the Anthropometry Quality Assurance and Quality Control (QAQC) SOP. These SOPs describe in detail the required equipment (including test kit models) and instructions for equipment calibration and maintenance, biological specimen collection, specimen processing, sample management, and results reporting. Participating laboratories will also perform scheduled quality checks and were required to enroll in the United Kingdom National External Quality Assessment Scheme (UK NEQAS) for hematology. In addition, for the purposes of this substudy protocol, the five-part differential hemoglobin analyzer and Masimo device will be routinely calibrated according to the company's guidelines. Each Masimo device user will receive training from the company, and we will maintain a daily use log as outlined in the SOP.

**
*Corrective action*
**

SpHb: Cases with reference errors (difference between the SpHb and CBC measurements greater than 0.5 g/dL, missing paired CBC reading), user errors (incorrect device setting) and problematic signal quality checks (low signal stability, low performance improvement quality (low perfusion), low SpHb confidence (ambient light interference) - indicated as spot-check monitoring results on the instrument) will be recorded to quantify the percent of cases with failure using lab-designated SOPs.

If there are errors related to CBC, samples should be re-run in case of any errors. If errors persist, lab designated SOPs (such as a daily QC log) will be used to document the errors and appropriate personnel will be notified. Issues related to blood draw (e.g., hemolysis) will be documented for corrective actions, but more blood will not be drawn.

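### The 19 pairs come from a t-test of zero mean shift and do not support studying agreement at a gestational age; 900 per site is ample but is justified by that test, not by agreement precision

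*Protocol article*

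**What the plan says.** Under Aim and objectives, the article asks whether SpHb measures "are accurate as compared to gold standard CBC laboratory tests using peripheral venous blood samples". The abstract says "The primary objective is to assess agreement between Masimo total hemoglobin and complete blood count", and Objective 1 of the analysis section does this with the ICC and Bland-Altman limits of agreement.

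Sample size considerations has three parts.

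- **Total sample size.** "The total sample size of 900 per study site will give 90% power for site-specific analyses to detect a systematic shift" of 0.108 SD, and 80% power for 0.093 SD. The test is named: "the probability that we will detect such a systematic shift using one sample t-test with significance level 0.05 is 90" percent. The text then adds: "Based on our pilot data from Kenya and Pakistan, the mean difference between SpHb and CBC is approximately 0.8 times its SD", so that 19 pairs would give 90% power. A second argument for 900 lists the chance of catching the largest 1%, 0.5%, 0.3%, 0.2% and 0.1% of differences.
- **Strata sample size.** This repeats 19 pairs at 0.8 SD for 90% power, with a null hypothesis of zero difference. The next sentence gives 33 pairs at 0.5 SD and states no other power.
- **Repeated measures.** This says that repeat measurements will come from 19 participants, and that discrepancy or agreement can be studied at a specific gestational age "given there are 19 matched pairs of data at any given time".

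**The concern.** A test of zero mean shift and an assessment of agreement have different targets. The test looks only at the mean of the differences. Limits of agreement also depend on their scatter, and precision for the scatter needs its own calculation. Rejecting zero shows some bias, which may be small. Failing to reject does not show agreement.

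The sample size that the test asks for also falls as the bias grows. A large pilot shift therefore makes 19 pairs look sufficient, although 19 pairs say little about where the limits of agreement lie. What is at stake is the Repeated measures sentence: it licenses agreement statements at a gestational age from a number that was never derived for agreement.

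**Working it through.** **1. Reproduce the plan's power figures.** Inputs from Sample size considerations: one-sample t-test, alpha 0.05 (sidedness not stated; two-sided reproduces the figures and one-sided does not), effect d in SD units. Power comes from the noncentral t distribution with noncentrality d·√n.

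| n | d | d·√n | Power found | Power stated |
|---|---|---|---|---|
| 900 | 0.108 | 3.24 | 89.9% | 90% |
| 900 | 0.093 | 2.79 | 79.6% | 80% |
| 19 | 0.8 | 3.49 | 90.9% | 90% |
| 33 | 0.5 | 2.87 | 79.5% | none given; the sentence before says 90% |

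The first three rows agree with the article, and 19 is the exact minimum for 90% at 0.8 SD. The fourth does not fit 90%: at 0.5 SD, 90% power needs 44 pairs and 80% needs 34.

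**2. The extreme-value argument.** The listed probabilities equal 1 − (1 − p)^900:

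- p = 0.01: 99.99%
- p = 0.005: 98.90%
- p = 0.003: 93.31%
- p = 0.002: 83.50%
- p = 0.001: 59.36%

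All five reproduce. Each is the chance that at least one pair falls in the top fraction p of its own distribution. The formula contains neither bias nor SD, so the result is the same for a good or a poor device. It does not size agreement.

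**3. Precision for agreement.** Assume normal differences and independent pairs, that is, one pair per woman at one visit. In units of the SD of the differences:

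- mean difference: half-width = t(0.975, n−1) / √n
- each limit of agreement: half-width = t(0.975, n−1) × √(1/n + 1.96²/(2(n−1)))

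For n = 19, t = 2.101:

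- mean: 2.101/√19 = 0.48 SD
- limit: 2.101 × √(0.0526 + 0.1067) = 2.101 × 0.399 = 0.84 SD

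For n = 900, t = 1.963:

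- mean: 1.963/30 = 0.065 SD
- limit: 1.963 × √(0.00111 + 0.00214) = 1.963 × 0.0570 = 0.11 SD

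| Pairs | Mean difference | Each limit of agreement |
|---|---|---|
| 19 | ±0.48 SD | ±0.84 SD |
| 33 | ±0.36 SD | ±0.61 SD |
| 900 | ±0.065 SD | ±0.11 SD |

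**4. What this means at the pilot shift.** With a mean difference of 0.8 SD, the limits of agreement are 0.8 − 1.96 = −1.16 SD and 0.8 + 1.96 = 2.76 SD. With 19 pairs the interval for the upper limit is 2.76 ± 0.84, or 1.92 to 3.60 SD. With 900 it is 2.76 ± 0.11, or 2.65 to 2.87 SD. With 19 pairs, each limit is uncertain by slightly more than the whole pilot bias.

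**The case against.** The sponsor can fairly say that systematic deviation is a named part of Objective 1, that Bland-Altman analysis reports the mean difference, and that sizing one component is legitimate. That stands, and it is why the zero-shift power can stay as a secondary statement. The sponsor can also say that 900 women per site are planned across five visits, so overall visit-level estimates will not in practice rest on 19 pairs. That stands too, and limits the harm. It does not make the 19-pair sentence true.

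A reader might infer four stronger points, which the documents do not support.

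- *That 900 is too small or arbitrary.* It is ample: ±0.11 SD for each limit. Only an agreement-based reason for it is absent from the section.
- *That the pilot settles the test in advance.* The article gives about 0.8 SD for Kenya and Pakistan, with no pilot sample size or interval and nothing for Zambia, while the power is claimed site by site.
- *That the t-test will serve as the verdict on accuracy.* It appears only in the sample size section. The Objective 1 analyses are estimates.
- *That an acceptance limit is missing and 0.5 g/dL should fill the gap.* A limit may stand in a fuller document that is not shown. The flag under Corrective action, "difference between the SpHb and CBC measurements greater than 0.5 g/dL", records errors and does not define acceptable agreement. As a pass rule for both limits with their intervals, it would need an SD of differences below 0.5/(2.76 + 0.11) ≈ 0.17 g/dL at the pilot shift, and below 0.5/(1.96 + 0.11) ≈ 0.24 g/dL even with no bias.

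**Conclusion.** The point holds in a limited form. The power calculations for 900 and 19 are arithmetically correct but answer whether the mean shift is zero, while the primary objective is agreement. The statement that agreement at a gestational age can be studied with 19 matched pairs is unsupported: each limit of agreement would carry about ±0.84 SD, some 7.5 times the ±0.11 SD that 900 pairs give (0.839/0.112). Two further statements in the section need correction. The 19 participants for repeat measurements conflict with 900 per site, and 33 pairs at 0.5 SD give 79.5% power, not the 90% of the sentence before.

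The precision figures assume normal differences, independent pairs within a visit and, for the 900 figure, complete pairs. Missed visits would widen it. They are in SD units because the article gives no SD of the differences in g/dL.

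**What to change.** In Sample size considerations:

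1. Justify 900 per site by precision: with 900 complete pairs at a visit, each limit of agreement is estimated to about ±0.11 SD and the mean difference to about ±0.065 SD.
2. Keep the zero-shift power as a secondary statement for the bias component, and do not present the extreme-value probabilities as support for agreement.
3. Delete the claim that 19 pairs suffice to study agreement at a gestational age, or print ±0.84 SD (limits) and ±0.48 SD (mean) beside it.
4. Reconcile the 19 participants in the Repeated measures paragraph with the 900 per site.
5. For 0.5 SD, either give 44 pairs for 90% power, or keep 33 and state about 80%.

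The cost is wording only, with no extra participants or visits. The small-sample statements become less favourable.

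### The 33 pairs given for a 0.5 SD shift in an anemia stratum carry about 80% power, not the 90% set one sentence earlier (44 needed); the 19 participants and three repeats also conflict with the design

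*Protocol article*

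**What the plan says.** All of this is in the protocol article.

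- **Sample size considerations, Total sample size.** The test is a one-sample t-test on the paired SpHb minus CBC differences at significance level 0.05. With 900 women per site it is said to give 90% power for a shift of 0.108 SD and 80% power for 0.093 SD. The text adds: "Based on our pilot data from Kenya and Pakistan, the mean difference between SpHb and CBC is approximately 0.8 times its SD". When it turns to the chance of catching extreme differences, it describes the data as follows: "With three repeated measures from each of the 900 participants".
- **Strata sample size.** The rule is "the Type I error probability is set at 0.05", with normally distributed differences. The first case is "If the true difference in the mean response of matched pairs is 0.8*SD, we will need to study 19 pairs of subjects" in order to "reject the null hypothesis that this response difference is zero with probability (power) 0.90". The second case follows at once: "When the mean difference is 0.5*SD, we would require a sample size of 33 pairs in the strata".
- **Repeated measures.** "We plan to collect repeated measurements from 19 participants at different time points". Visit-specific study of agreement is then said to be possible given 19 matched pairs at a time point.
- **Study design and Recruitment of participants.** Five timepoints, with an additional week 32 measurement in Pakistan; 900 women per site, 2700 in total.

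**The concern.** The two stratum figures stand next to each other, and only the effect size changes between them. A reader will carry the 0.90 power over to the 33 pairs, because no other power appears in that paragraph and the next one again speaks of 90%. If 33 does not deliver 90%, a small stratum (severe anemia is the obvious case) could be judged adequately filled at 33 pairs when the chance of missing a 0.5 SD shift is about 20% rather than 10%.

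The paragraph on repeated measures adds to the confusion. It presents the minimum from the 0.8 SD calculation as the number of women to be followed, and it links that number to agreement at a given gestational age. Rejecting a mean shift of zero and assessing agreement are different tasks, and 19 pairs were derived only for the first.

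**Working it through.** **Inputs.** Type I error 0.05, one-sample t-test on paired differences, power 0.90 at 0.8 SD with 19 pairs, and 33 pairs at 0.5 SD, all from Sample size considerations. Sidedness is not stated; step 1 shows that it is two-sided.

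**Formula.** For n pairs and a shift of d SD, the t statistic is noncentral t with n − 1 degrees of freedom and noncentrality d√n. Power is the probability that its absolute value exceeds the 97.5% point of central t.

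**Step 1: reproduce the plan's own figures.**

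| n | d | d√n | Two-sided power | Plan states |
|---|---|---|---|---|
| 18 | 0.8 | 3.394 | 89.2% | – |
| 19 | 0.8 | 3.487 | 90.9% | 90% |
| 900 | 0.108 | 3.240 | 89.9% | 90% |
| 900 | 0.093 | 2.790 | 79.6% | 80% |

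All three stated figures are recovered, and 19 is the smallest n that reaches 90% at 0.8 SD. A one-sided test would need only 15 pairs there, so the plan's method is two-sided.

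**Step 2: apply the same method at 0.5 SD.**

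| n | d√n | Two-sided power |
|---|---|---|
| 33 | 2.872 | 79.5% |
| 34 | 2.915 | 80.8% |
| 43 | 3.279 | 89.3% |
| 44 | 3.317 | 90.0% |

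So 90% power needs 44 pairs and 80% needs 34. The miss rate at 33 pairs is 100 − 79.5 = 20.5%. At 90% power, 33 pairs detect about 0.58 SD.

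**Step 3: try other routes to 33.**

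- Normal approximation, two-sided, 90%: (1.960 + 1.282)² / 0.5² = 42.0, which rounds up to 43.
- Normal approximation, two-sided, 80%: (1.960 + 0.842)² / 0.5² = 31.4, which rounds up to 32.
- Exact one-sided t: 87.8% power at 33 pairs, with 36 needed for 90%.
- One-sided normal approximation at 90%: 35 pairs. The same formula gives 14, not 19, at 0.8 SD, so it is not the plan's method.

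Of these, 33 fits only a two-sided calculation at about 80% power.

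**Step 4: set the counts side by side.**

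| Item | Sample size section | Design and recruitment sections |
|---|---|---|
| Women with repeated measurements | 19 (Repeated measures); 900 (Total sample size) | 900 per site |
| Repeats per woman | 3 | 5 (6 in Pakistan) |

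**Step 5: does any stated number depend on the three repeats?** The extreme-value probabilities follow 1 − (1 − q)^900. For q = 1%, 0.5%, 0.3%, 0.2% and 0.1% this gives 99.99%, 98.90%, 93.31%, 83.50% and 59.36%, exactly as printed. They use one observation per woman, so the number of repeats enters none of them.

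**The case against.** The strongest reply is that the 33-pair sentence names no power. The section reports 80% as well as 90% for its 900-woman calculation, and it rounds 79.6% to 80% there; by the same rounding 33 pairs (79.5%) would be an 80% figure. A sample-size curve is also mentioned that is not in the text available here, and it may carry a label. Part of this stands: the 90% is carried over from the preceding sentence, and the defect may be a missing label rather than a wrong n. But the 80% for 900 women is labelled and this one is not. No curve can make 33 pairs yield 90% at 0.5 SD.

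It is also fair to say that no quota, stopping rule or analysis depends on 33, that the strata calculation is offered as speculative, and that 19 matched pairs at a visit can be read as a minimum condition rather than as the planned data. These points limit the impact. They do not reconcile 19 participants with 900 per site.

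Three stronger readings are tempting and are not supported:

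- **That every figure in the section powers a test of zero shift.** The five extreme-value probabilities test no shift; they concern the tails of the differences.
- **That the pilot has already rejected zero shift.** The article gives the pilot ratio of about 0.8 but no pilot sample size, and the pilot covers only Kenya and Pakistan.
- **That the plan is deficient without a precision target for the limits of agreement.** A condensed article may leave this to the full plan. A figure based on 900 independent single pairs would also not match the repeated-measures variances planned for the Bland–Altman analysis.

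**Conclusion.** The 33-pair figure is wrong as it reads. Under the only power the strata paragraph gives (0.90, two-sided 0.05), a 0.5 SD shift needs 44 pairs, 11 more than stated, and 33 pairs give 79.5%. If 80% was intended, the text does not say so, and the exact requirement is 34. The result rests on normally distributed differences and one independent pair per woman, as the plan's own calculation does.

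The 19 participants contradict the 900 per site, and the three repeats contradict the five timepoints (six in Pakistan); the latter is a slip with no numerical consequence. Site-level power is sound. The effect is confined to small anemia strata, and to a reader who takes 19 pairs at a visit as enough to assess agreement.

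**What to change.** In Sample size considerations:

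1. **Strata sample size.** Change 33 to 44, or keep 33 and say that it gives about 80% power (exactly 34 for 80%). State that the test is two-sided.
2. **Repeated measures.** Replace the 19 participants with the planned 900 per site. Describe 19 matched pairs at a time point only as the minimum for detecting a 0.8 SD mean shift with 90% power, not as sufficient to assess agreement.
3. **Total sample size.** Change three repeated measures to five, six in Pakistan. The listed probabilities stay as they are.

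The cost is a wording correction. Under the first option in item 1, one stated figure becomes less favourable. Enrolment, visits and analyses do not change.
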